#### Missing data

All communities experience in-migration and out-migration. We will add new arrivals to the study but will not follow those leaving the household clusters. There is no reason to expect differential out-migration between intervention and control clusters. Self-selection (decision not to participate or not to answer certain questions) is a concern, given the structured engagement implied by the intervention. Those who opt not to respond may be less involved with dengue control – thus reducing the measured effect. We will analyse missing data using Amelia II [29] to impute values for missing data with an EM algorithm for the primary outcome (serological evidence of recent dengue virus infection). Estimates will reconcile data from ten imputed data sets using Rubin’s approach [30] in the R package Zelig [31].

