#### Adherence/compliance rates

The total 3,217 households with children aged 3–9 years yielded 2,992 saliva samples from these children (7% or 225 declined or were not present at the time of the visit). By the fourth year of the feasibility study (2007), twice as many households in the intervention sites (15.5%) as in the control sites (7.1%) said they participated directly in community dengue control exercises, and 50.7% in intervention and 39.5% in control sites reported having looked for larvae in their water stores over the last week.

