### Outcomes

The main outcome measures are (i) risk of dengue virus infection as measured by a minimum of two-fold increase in anti-dengue virus IgG antibodies across paired saliva samples collected before and after the 2012 dengue season in children aged 3–9 years [20] (ii) dengue cases (any age) in the last year reported by the household respondent; and (iii) entomological indices of *Aedes aegypti* breeding sites, using the protocol developed in the Nicaragua feasibility study [21].

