#### Principal analysis

With 150 clusters allocated evenly between intervention and control arms, the cluster analysis of primary outcomes will rest on a t-test, following an intention-to-treat principle (everyone included in each cluster, per allocation). The simultaneous evaluation in control and intervention sites will account for temporal effects. Serological status, reports of dengue illness, and vector indices lend themselves to analysis as continuous variables. Recent infection in children, adopting a cut-off of a two-fold increase of IgG units between samples, and pupae-positive households, are both dichotomized variables; the percent of households with serological evidence of recent infection in any child or with larvae/pupae-positive entomology serves as a continuous variable in each site. We will report outcomes as absolute event rates among intervention and control groups, with relative risk reduction (RRR) and 95% confidence intervals.

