### Power calculation

Data from the feasibility study in Managua facilitated sample size estimation. Using the dengue serology results as the principal outcome, control communities in 2004–8 showed a range of 1.5% to 7.4% (k-statistic 0.328). Follow-up of 40 children in each of 150 clusters (75 clusters per arm) would detect a 33.3% reduction in incidence (4.5% to 3%) with 80% power at a significance level of 5%. These calculations assume no interaction effects and a two-sided test with cluster as unit of primary analysis in unmatched parallel groups. Calculations used a spreadsheet based on the trial simulator devised by Taylor and colleagues [35].

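### The protocol names a normal-theory imputer (Amelia II) for a rare yes/no outcome in clustered children; if its draws are turned into 0/1 values, the event rates, and on some routes the relative risk reduction, can be biased

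*Protocol article*

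**What the plan says.** The Missing data section of the protocol article commits to a method: "We will analyse missing data using Amelia II [29] to impute values for missing data with an EM algorithm for the primary outcome", identified there as the serological one. It adds "Estimates will reconcile data from ten imputed data sets", pooled by Rubin's approach in the R package Zelig.

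The outcome is defined under Outcomes as "a minimum of two-fold increase in anti-dengue virus IgG antibodies across paired saliva samples". The Principal analysis section makes it binary for each child: "Recent infection in children, adopting a cut-off of a two-fold increase of IgG units between samples, and pupae-positive households, are both dichotomized variables". The percentage of households with such evidence in any child then "serves as a continuous variable in each site" and is compared by t-test. The Secondary analysis section fits individual-level models, either a non-linear mixed model with odds ratios or a GLMM with cluster as a random effect.

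The Power calculation section plans 75 clusters per arm, 40 children each, 4.5% versus 3%, k = 0.328. The only missing-sample figure comes from the feasibility study, for one visit: "7% or 225 declined or were not present at the time of the visit".

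**The concern.** A multivariate normal model describes a 4.5% yes/no variable poorly: a large share of its draws are negative. Two uses in the protocol cannot take such values. A household counted as positive if any child is positive needs a yes or no for each child, and an odds-ratio model or binary GLMM needs 0/1 data. The likely next step is therefore to convert the draws, and the usual conversions do not return the original rate. The article promises absolute event rates and an RRR with a 95% interval, so an error introduced by the imputation would reach the headline result even if samples were missing completely at random. Amelia II also has no random cluster effect, while the trial is analysed by cluster.

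**Working it through.** **Inputs.** From Power calculation: p0 = 0.045, p1 = 0.03, m = 40, 75 clusters per arm, k = 0.328, two-sided 5%, 80% power. From Adherence/compliance rates: 225/3,217 = 7.0% of samples missing at one visit. Assumed: 7% lost independently at each of two visits, so 1 − 0.93² = 13.5% of pairs missing; 20% and 40% as a wider range; missing completely at random. That Amelia II is single-level and multivariate normal is general knowledge of the software, not a statement in the article.

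**1. The plan's own figure.** c = 1 + (1.960 + 0.842)² × [p0(1−p0)/m + p1(1−p1)/m + k²(p0² + p1²)]/(p0−p1)² = 1 + 7.849 × (0.001802 + 0.000315)/0.000225 = 74.8. The stated 75 clusters per arm are reproduced.

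**2. Fit of the normal model.** With SD √(0.045 × 0.955) = 0.207, P(draw < 0) = Φ(−0.045/0.207) = 41%. At 3%, with SD 0.171, it is 43%.

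**3. What conversion does to imputed children.** A normal model with arm as a predictor has one residual SD: s = √[(0.0430 + 0.0291)/2] = 0.190.
- Clip to 0–1, then draw an event. The mean is approximately p·Φ(p/s) + s·φ(p/s), which gives 10.0% (control) and 9.2% (intervention). If each arm has its own SD, the figures are 10.7% and 8.4%.
- Round at 0.5. The mean is 1 − Φ((0.5 − p)/s), which gives 0.83% and 0.66%.
- Omit arm, do not convert. Both arms receive the pooled mean, 3.75%.

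**4. Final rates.** With a share f missing, the rate is (1 − f)p + f × (imputed rate). Example at f = 0.135, clipped: control 0.865 × 4.5 + 0.135 × 10.0 = 5.25%; intervention 0.865 × 3.0 + 0.135 × 9.2 = 3.83%; RRR = 1 − 3.83/5.25 = 27%.

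| Missing | Clip and draw | Round at 0.5 | Arm omitted, unconverted |
|---|---|---|---|
| 7% | 4.89 / 3.43, RRR 29.8% | 4.24 / 2.84, RRR 33.1% | 4.45 / 3.05, RRR 31.4% |
| 13.5% | 5.25 / 3.83, RRR 27.0% | 4.00 / 2.68, RRR 33.0% | 4.40 / 3.10, RRR 29.5% |
| 20% | 5.61 / 4.23, RRR 24.5% | 3.77 / 2.53, RRR 32.7% | 4.35 / 3.15, RRR 27.6% |

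(Control / intervention rates in %.)

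**5. Simulation of the cluster t-test.** 800 trials per setting, beta-distributed cluster rates with k = 0.328, ten imputations, Rubin pooling. This emulates single-level normal imputation; Amelia II itself was not run. Results at 7%, 20% and 40% missing:
- Clip and draw: RRR 29.9%, 24.6%, 18.4%; power 70%, 53%, 22%. Complete cases give power 77%, 73%, 58%, so on this route imputing is worse than not imputing.
- Rounding: RRR 33.1%, 33.0%, 31.4%; coverage of the risk difference 93%, 92%, 76%.
- Unconverted, arm included: RRR 33.4%, 33.6%, 32.9%; coverage 94%, 95%, 95%.
- Cluster-aware binary imputation by arm (beta-binomial, k taken as known): RRR 33.3%, 33.7%, 33.0%; coverage 95%, 96%, 96%.

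**6. Clusters.** The planning k implies an intraclass correlation of k²p0/(1 − p0) = 0.1076 × 0.045/0.955 = 0.005. The single-level SE is only about 1–2% below the cluster-aware one.

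**The case against.** The principal analysis is a t-test on a site percentage treated as continuous, so nothing in it forces draws to be clipped or rounded. Left as they are, with arm in the model, they give nearly correct rates, RRR and coverage. The article does not say that the yes/no variable is what gets imputed: IgG units are continuous, and the planned three- and four-fold analyses require them to be kept. It does not exclude arm or site from the imputation model, and a condensed article may leave such details to an analysis plan.

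Much of this stands. A reader might infer that the rates, the RRR and its interval must come out wrong, or that the method fails under any handling; the simulation of unconverted draws contradicts both. A reader might also infer that rounding inflates the RRR (to 35.5% at 13.5% missing). That appears only if each arm has its own SD and disappears with a common one. Nor does the lack of a cluster term do much damage at the planning k.

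The objection does not remove the point. The imputer is a choice the article states, not a detail it omits. Unconverted draws do not serve the any-child household rule or the binary models: a draw of −0.12 or 0.3 is neither yes nor no.

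**Conclusion.** The point holds as a conditional one. The named method does not suit a rare binary outcome, and the article's own household rule and secondary models make conversion to 0/1 likely. On the clip-and-draw route the RRR falls from 33.3% to about 30%, 27% and 24.5% at 7%, 13.5% and 20% missing. Rounding biases the absolute rates and leaves the RRR near 33%; omitting arm attenuates the RRR. At the only documented missing rate, 7%, the worst route with arm included moves the RRR by about 3 points; larger shifts need more missing pairs. That is plausible, since the outcome needs two samples and the Missing data section does not follow people who leave, but it is not documented.

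The figures assume data missing completely at random, the planning rates, and k = 0.328. The feasibility ICC of 0.78 for saliva samples would make clustering far more important, but it cannot be squared with that k and is a separate matter.

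**What to change.** Replace the Amelia II sentence under Missing data with the following:
- Multiply impute the child's yes/no outcome with a two-level logistic model (random cluster intercept), fitted by arm or including arm, with stratum, age, household covariates and the observed pre-season IgG value as predictors.
- Do not clip or round normal draws.
- In each of the ten data sets, form the household and cluster percentages, run the same cluster-level t-test, and pool by Rubin's rules.

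If IgG units are imputed instead, so that the two-, three- and four-fold analyses agree with each other, use a method that does not assume normality, such as predictive mean matching. The antibody-unit formula under Serology samples subtracts the negative control, so units can be zero or negative and logs undefined. A normal model for log units in a mixture of infected and uninfected children can also misstate the share with a two-fold rise.

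The cost is wording and code, a little more computing, and possibly a slightly wider interval.

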#### Economic analysis

The sample size estimate for this trial uses relatively rare primary outcomes, so it will be adequately powered to consider economic implications of the intervention, which could be profound. Informed community mobilisation could reduce dengue rates directly but, by increasing social engagement, it could also increase the proportion of the population enabled to benefit from other prevention interventions, increasing their impact correspondingly. The dengue virus infection end-point (serology) is most relevant for economic analysis of the direct impact, although reduction of entomological indices also has resonance. By costing the intervention, it should be possible to document the costs of dengue cases avoided [32]. Documenting the real cost of preventing dengue will be less simple. A cost-benefit approach will be relevant, with benefits identified and qualified by communities themselves. Individuals who opt to reduce their own dengue risk probably do so based on perceived costs and benefits of prevention – we have called this the individual “cost benefit equation” [33]. This equation can lead to very different decisions from those imagined by dengue control programmes, especially in the context of abatización, which removes choice and changes the way people estimate their own value in the choices they make.

#### Implications for health services

The case to be made is that informed community mobilisation reduces dengue risks, without reliance on imported pesticide. A secondary case is that the costs compare favourably with the gains of doing this; pesticide-free prevention requires less treatment of cases, less work time lost, and less importation of expensive pesticides.

#### Software

CIETmap [34] is a hybrid vector-raster GIS software with seamless linkages between epidemiological analysis and mapping. The package provides a windows-like interface with the popular open-source statistical programming language R.

### Power calculation

Data from the feasibility study in Managua facilitated sample size estimation. Using the dengue serology results as the principal outcome, control communities in 2004–8 showed a range of 1.5% to 7.4% (k-statistic 0.328). Follow-up of 40 children in each of 150 clusters (75 clusters per arm) would detect a 33.3% reduction in incidence (4.5% to 3%) with 80% power at a significance level of 5%. These calculations assume no interaction effects and a two-sided test with cluster as unit of primary analysis in unmatched parallel groups. Calculations used a spreadsheet based on the trial simulator devised by Taylor and colleagues [35].

### Randomisation

#### Allocation concealment

Randomisation will be conducted centrally by a sampling statistician who is not engaged in the rest of the study. Computer-generated random numbers will determine intervention status in each stratum, defined by the baseline study. The intervention will begin promptly after randomisation with disclosure of intervention status at that time.

#### Blinding

The prevention efforts will be obvious to residents in the intervention sites, and some outcomes (particularly conscious knowledge) could be influenced by knowledge of intervention status. The main outcome indicators (reduction in serological evidence of recent dengue virus infection or entomological indices) would be less susceptible to this bias. To prevent potential bias, interviewers should ideally be unaware if they are interviewing in intervention or control clusters. Data managers will be unaware of intervention status of clusters.

#### Contamination

There may be some contamination of the control clusters: through people interacting between the clusters at the individual or household level; through schools (children from control clusters going to schools in the intervention clusters); and through local government or NGOs taking up the emerging evidence to guide interventions in control clusters. Perhaps a bigger concern, in urban areas, is that mosquitoes from neighbouring households influence rates in the intervention sites and that children may get bitten by infected mosquitoes outside of their intervention site [36, 37]. Both types of contamination will reduce the measured difference between control and intervention clusters. We cannot avoid this effect. We will document spread of the intervention beyond the sites in several regards: (i) mechanisms for generalising evidence, (ii) uptake at policy level and in the public discourse, (iii) new initiatives or changes in approach by agencies involved in dengue control, and (iv) impact in the control clusters as well as in the intervention clusters.

### Ethical considerations

#### Ethical review

The Institutional Review Board (IRB) at the University of California, Berkeley, and the CIET IRB reviewed the Nicaraguan arm. The Research Ethics Board of CIETcanada and the Ethics Committee of the Centro de Investigación de Enfermedades Tropicales at the *Universidad Autónoma de Guerrero* reviewed the Mexican arm.Informed consent: Using a standard script, in the household survey, interviewers explain to respondents the nature of the survey, its voluntary character, and the anonymous quality of the process. They explain that respondents may decline to answer any questions they do not wish to, and may terminate the interview at any time. They then ask respondents for their consent to conduct the interview.Samples: Separate informed consent is obtained from a parent or guardian for collecting the saliva samples with assurance that the results will be returned to them. To allow linkage of the repeat sample result with individual risk factors from the questionnaire responses, we use adhesive labels with ID codes fixed to the sample, to the completed questionnaire and, in the case of Nicaragua, to an administrative sheet that includes the date and time of the sample.Ensuring confidentiality: Training of fieldworkers and data operators will emphasize responsibility for maintaining confidentiality of all information to which they have access during the work. We will report only grouped findings, in a way that does not allow identification of any individuals or individual communities. In the household survey, no names or identifiers will be recorded next to individual responses. Unique number labels will be used to link saliva specimens to questionnaire responses, without identifying the person by name. In individual follow-up for repeat samples, we will record the name of the child in order to match this from visit to visit and to be able to deliver results of the tests to parents or guardians. In focus groups, no names of focus group participants will be recorded, and reports of focus group findings will not identify individual communities.
4.Protection of emotional well-being: We do not expect the questions to awaken distressing memories. To the contrary, we expect the opportunity to engage in household and community protection to be uplifting and self-affirming.5.Normative pressure within communities: Both the CIETinternational and CIETcanada ethical review boards raised questions regarding possible stigmatising of residents who failed to participate in community vector control activities. Both boards were satisfied by the responses they received from the field teams on this subject. We will prepare a full discussion of the ethical issues and our position regarding them and submit it for publication in a peer-reviewed journal.6.Security of data: Digital records will be secure and accessible only to the lead epidemiologist. Original paper records will be securely transported, stored, retained and finally destroyed in accordance with CIET guidelines for security, storage and eventual destruction of paper records [38].7.Promotion of equal opportunities: At least one half of field workers in the interview teams and the local action teams will be women. The field team leader in Mexico, [name], is a member of the CIET academic council. [name] is the nominated principal investigator of the Nicaragua team.

## Discussion

Current dengue control measures in Latin America rest on an organophosphate pesticide, temephos (Abate), inserted in the household water storage containers that are often breeding sites for *Aedes aegypti*, the main vector for dengue virus in the region. Many national governments have used temephos in household water stores. The WHO approval to do so [39, 40] cites the lack of evidence of toxicity.

Temephos is not licensed for human consumption in the USA [41]; the US Environmental Protection Agency says temephos “…has no food uses, is not likely to be found in drinking water, and is not used in or around homes or areas that children frequent” [42]. Studies not sponsored by the producers have documented animal toxicity [43, 44] and genotoxicity [45]. Resistance of the mosquito to this pesticide is already well documented and is a growing concern, given the variable coverage and consistency of many government-initiated programmes using temephos for dengue control [46–52]. We could not identify any community-based randomised controlled trials showing a protective effect of temephos against dengue virus infection.

Given the current government commitment to temephos, it will take a while to generate full participation of state and local authorities. Assuming the intervention is successful, there is an ethical obligation to implement it also in control communities. As this is unlikely within the 3-year time period of this project, other funds will be sought for that purpose.

There is also a strong community-building component integrated into the trial design; one of the goals is to measure the impact of the intervention on social capital. In each intervention cluster, the community action team will be trained in evidence-based communication as well as in ways of engaging with residents that are fully respectful of personal and community autonomy.
